**Discussion:**

The slow rate of recruitment is an ongoing practical issue. There is a limitation to the number of eligible patients compared to what was predicted, mainly due to the nature of this patient group. After a substantial amendment to widen inclusion criteria and reduce the baseline period to 7 days for patients with a high seizure burden, the rate of recruitment steadily increased. A number of operational concerns regarding dietetic time were also highlighted impacting on the recruitment rate. However, the combination of a low dropout rate and the opening of further centres, the trial should successfully meet the final recruitment target. All nine centres are now recruiting and we hope to open further centres within the UK.

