### Sample size

For the primary outcome variable, based on data from Neal et al., [17], we used mean percentage change in seizures from baseline of 62% (SD 45) in the KD group, assuming a change of 90% in the control group (SD 50) (100 = no change in frequency of seizures from baseline) at 90% power and 5% significance. This gives a sample size of 61 in each group (122 in total). Accounting for a 10% dropout rate, gives 68 in each group (136 in total), and inflation for a therapist effect (dietitian) to one group, assuming nine centres, with an average cluster size of eight and an intracluster correlation coefficient (ICC) of 0.05, the inflation factor is 1.35, giving 92 in the KD group and 68 in the control group (160 in total). If dropout was 20%, this sample size would still have 86% power.

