### Deliverability and feasibility

An initial pilot study involving two centres over 12 months will aim to recruit approximately 20% of the total sample required: 35 participants over 12 months.

The pilot study will run in two centres in London: Great Ormond Street Hospital for Children and Evelina London Children’s Hospital over the initial 12 months. We will aim to assess approximately 50 eligible patients in this time frame. Additionally, adverse events (AEs) will be monitored and data on safety will be reviewed. We will progress to the full study if the following are achieved:Achieving a 60% recruitment rate; 30 families agreeing to randomisationNo more than 10 (29%) failing to complete the 8-week trial period

The main study will proceed to include recruitment from the further seven centres should the above criteria be met. Recruitment will be expected at a rate of 28/year from GOSH, and approximately 7/year from the remaining seven centres (total 84/year). This enables a completed primary outcome in the desired 160 children.

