### Trial status

The trial was initiated in the pilot phase on 1 February 2015 and is currently recruiting in the full trial phase across nine centres. We are in the process of initiating further centres as part of the next amendment. Twenty-nine patients have been randomised to date and the planned recruitment end date is July 2018.

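### The 1.35 inflation factor assumes nine equal clusters of eight, which fits neither the 92-child KD arm nor the planned centre sizes; power at 160 is about 88–89%, not 90%

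*Protocol article*

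**What the plan says.** The Sample size section of the Protocol article takes a "mean percentage change in seizures from baseline of 62% (SD 45) in the KD group". For the comparator arm the calculation proceeds by "assuming a change of 90% in the control group (SD 50"), and the trial is sized "at 90% power and 5% significance". This gives 61 per arm, then 68 per arm after 10% dropout. The KD arm alone is then inflated for clustering by dietitian: "assuming nine centres, with an average cluster size of eight and an intracluster correlation coefficient (ICC) of 0.05, the inflation factor is 1.35". The result is 92 KD and 68 control children, 160 in all, with 86% power claimed if dropout reaches 20%.

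The Deliverability and feasibility section describes two pilot centres followed by seven more. It expects "28/year from GOSH, and approximately 7/year from the remaining seven centres (total 84/year") and concludes: "This enables a completed primary outcome in the desired 160 children".

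The Statistical analysis section treats centre as synonymous with therapist and includes it as a random effect in a Poisson mixed model.

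**The concern.** The inflation factor depends on how many KD children each centre treats, and two parts of the article disagree with the value used. Nine centres of eight make 72 children, whereas the factor is used to arrive at 92. The recruitment plan also puts a third of the children (28 of 84) in one centre. For a given mean cluster size, unequal clusters give a larger variance inflation than equal ones, so a factor built on equal clusters is too small. The stated power at 160, and at 20% dropout, would then be somewhat optimistic.

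Two figures in the recruitment paragraph also conflict with their own components: the yearly total, and the description of 160 as children with a completed outcome when the Sample size section has already added dropout to reach 160.

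**Working it through.** **Inputs.** From Sample size: means 62 and 90 (difference 28), SDs 45 and 50, 5% significance (taken as two-sided, which reproduces the plan's figure), 90% power, 10% or 20% dropout, nine centres, ICC 0.05. From Deliverability and feasibility: 28 per year at one centre and 7 per year at each of the others.

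**1. The plan's own chain.**
- Per arm: (1.960 + 1.282)² × (45² + 50²) / 28² = 60.6, so 61.
- Dropout: 61 / 0.9 = 67.8, so 68.
- Factor: 1 + (8 − 1) × 0.05 = 1.35.
- KD arm: 68 × 1.35 = 91.8, so 92. Total 92 + 68 = 160.

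All steps reproduce. Power is Φ(28/SE − 1.96), with SE² = 45² × DE / n_KD + 50² / n_control, where DE is the design effect. With 10% dropout, n_KD = 82.8 and n_control = 61.2. DE 1.35 gives SE² = 33.02 + 40.85 = 73.87 and power 90.3%. With 20% dropout (73.6 and 54.4) it gives 86.7%. A noncentral t version gives 89.8% and 86.1%, which agrees with the stated 90% and 86%.

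**2. Where eight comes from.** 68/9 = 7.6, the arm before inflation. After inflation the mean is 92/9 = 10.2 enrolled, or 82.8/9 = 9.2 analysed. With nine equal centres and 10% dropout:
- 9.2 analysed: DE 1.41, power 89.7%.
- 10.2 enrolled: DE 1.46, power 89.2%.

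With 20% dropout the analysed mean is 73.6/9 = 8.2, DE is 1.36 and power is 86.6%. Correcting the mean alone therefore costs about one point at most.

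**3. Planned unequal centres.** Split the 82.8 analysed KD children 28:7, as one centre of 27.6 and eight of 6.9.
- Unweighted: the size-weighted mean cluster is (27.6² + 8 × 6.9²) / 82.8 = 1142.64 / 82.8 = 13.8, so DE = 1 + 12.8 × 0.05 = 1.64.
- Weighted by inverse variance: the information from a centre of size m is m / (1 + (m − 1) × 0.05). This is 27.6/2.33 = 11.85 for the large centre and 6.9/1.295 = 5.33 for each small one. The sum is 11.85 + 8 × 5.33 = 54.5, so DE = 82.8 / 54.5 = 1.52.

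| Case | DE, 10% dropout | Power | DE, 20% dropout | Power |
|---|---|---|---|---|
| Plan's factor | 1.35 | 90.3% | 1.35 | 86.7% |
| Nine equal centres, analysed size | 1.41 | 89.7% | 1.36 | 86.6% |
| 28:7 split, weighted | 1.52 | 88.7% | 1.46 | 85.5% |
| 28:7 split, unweighted | 1.64 | 87.5% | 1.56 | 84.3% |

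**4. Recruitment figures.** 28 + 7 × 7 = 77, whereas 28 + 8 × 7 = 84. Two pilot centres plus seven make nine, which is one at 28 and eight at 7. On the plan's 10% dropout, 160 × 0.9 = 144 children would have a completed primary outcome.

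**The case against.** The best defence is that the calculation contains no arithmetic error: every step follows from its stated inputs. That stands, and a reader who infers that 160 was wrongly derived goes too far.

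Correcting the mean cluster size alone is immaterial beside an assumed ICC of 0.05. About ten centres would bring the analysed mean back to roughly eight (82.8/10 = 8.3), and the article says further centres are planned. This also stands, but it does not address a third of recruitment coming from one centre.

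The unweighted 87.5% should not lead, because the planned analysis has a random centre effect and the weighted 88.7% is the nearer approximation. That is accepted.

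On the yearly total, 84 is probably right and the word seven wrong, with the second pilot centre left out of the sentence. Neither 77 nor 84 alters the sample size or the power. On the 160, the Discontinuation/withdrawal section keeps withdrawn children in scheduled follow-up, so stopping treatment does not by itself lose an outcome. Even so, the plan budgets 10% dropout within 160 and cannot also count 160 as completed.

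A reader might set "Twenty-nine patients have been randomised to date and the planned recruitment end date is July 2018" beside the claim that "the trial should successfully meet the final recruitment target" and infer that the trial will fall far short, with much lower power. The documents do not support that. The date of the count is not given. The average to that point includes a two-centre pilot, and the Abstract reports rising recruitment after an amendment. At 84 per year, 29 becomes 29 + 105 = 134 by July 2018 if 15 months remain (a count at publication in April 2017), but 29 + 168 = 197 if 24 months remain. Whether 160 is missed at the planned rate cannot be settled from the article.

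**Conclusion.** The point holds as a modest overstatement of power and two inconsistent recruitment figures. At 160 randomised with 10% dropout, power is about 88.7% (87.5% without weighting), against 90% stated. With 20% dropout it is about 85.5% (84.3%), against 86% stated. Compared with the same formula at factor 1.35 (90.3% and 86.7%), the loss is 1.2 to 2.8 points. Most of it comes from unequal centre sizes and little from the mean of eight.

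The figures assume an ICC of 0.05, nine centres with eight recruiting 7 per year (the second pilot centre has no stated rate of its own), a KD arm split in proportion to recruitment, and no added centres. Like the plan, they use a comparison of mean percentages with inflation in the KD arm only, so they approximate the Poisson mixed model and are not a calculation for it.

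**What to change.** - Recompute the inflation factor from the planned, unequal KD-arm centre sizes, and state whether size means enrolled or analysed children. Restate power at 160 as about 88–89% with 10% dropout and about 85% with 20%. If the centre list changes, use the updated sizes.
- In Deliverability and feasibility, reconcile the centre count with the yearly total: eight other centres if 84 is intended, or 77 if seven is.
- Describe 160 as randomised, with about 144 expected to have a completed primary outcome.

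The cost is slightly less favourable stated figures. No extra patients are needed.

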#### Treatment procedures

##### Trial arm 1

Classical ketogenic diet (KD arm)

The experimental intervention will be an 8-week trial of KD therapy. A KD intervention manual will be created and provided to sites to ensure consistency of the KD implementation across centres. The manual includes basic instructions on how to calculate the classical KD and advice regarding diet implementation such as supplementation, tube feeding, breastfeeding, weaning and fine-tuning the diet. Children allocated to KD therapy will have their diets individually calculated by a paediatric dietitian with consideration of daily calorie requirements, adequate protein intake for growth and vitamin and mineral supplementation. All diets will be implemented according to a classical KD protocol, i.e. based on a ratio of fat to carbohydrate and protein that will usually be between 2:1 and 4:1. In order to achieve a state of ketosis, meal plans have to be accurately calculated for each child individually and recorded in the patient’s medical notes. Breastfeeding can be continued on a KD, in combination with a ketogenic feed which will be given in a prescribed amount before each breastfeed. If breast milk is expressed, this can be mixed with the ketogenic feed to the correct macronutrient ratio. Infants on a KD can be weaned as per Department of Health guidelines [36], with advice given on how to adapt standard weaning foods by addition of extra fat.

Hospital stays will be determined by the clinical team at the treating centre, utilising the ‘Trial Intervention Manual’. A non-fasting initiation protocol will be used for all children. Parents or carers will attend a teaching session prior to diet commencement, including how to manage possible early side effects, such as excess ketosis and hypoglycaemia. Teaching of families in the KD arm will occur following randomisation and prior to starting the diet.

The KD to be implemented will be the classical KD, aiming for at least a 3:1 ratio (fat to carbohydrate and protein). This will be implemented according to a standard text [35]. Further, an initial workshop of dietitians will be led by [name] (co-principal investigator (PI)) in order to ensure consistency of implementation. Cross-site consistency of KD implementation will be monitored after the 8-week and 12-month visits by the dietetic assistant. Details to be monitored include the calculation of energy prescriptions, protein intake, teaching sessions, initiation regimes, supplementation and ketone levels. Monitoring Discrepancy Forms will be created and the Protocol Deviation Log completed, if appropriate.

##### Trial arm 2

Further antiepileptic drugs (AED arm)

The control intervention will be drug therapy with the most appropriate further AED for a particular child, depending on their presenting seizures, epilepsy syndrome and previous drugs used. This will be chosen by the expert clinician responsible for management of the participant’s epilepsy. Paediatric neurologists will meet at an initial workshop to discuss clinical practice with the aim of forming the basis of a consensus protocol to ensure the consistency of AED treatments delivered. The list of agreed drugs that may be utilised are described in Additional file 5. These are considered IMPs in this trial, irrespective of which arm of the trial the patient is randomised to. This is a pragmatic trial that uses authorised medicinal products for epilepsy within the European Economic Area (EEA). Although the majority of these IMPs are not licensed for paediatric use, or for use in this age group, they are used in routine care as part of established clinical practice. Patients who are prescribed products with no marketing authorisation (‘specials’) for epilepsy or AEDs not listed in the below table will not be eligible for this trial. The KD is not classed as a medicinal product and is not included in Additional file 5. The dietetic assistant will monitor cross-site consistency of IMP prescription according to the protocol.

A discussion about diet and healthy eating will be also be undertaken with families of infants randomised to the AED arm at the randomisation visit. If the participant is already under local dietetic support, it should be ensured that this monitoring continues. If the participant does not have local dietetic support but this is deemed necessary by the ketogenic dietitian, an appropriate referral should be made by the clinician. Otherwise, a very brief discussion about general infant or toddler nutrition will be had, including details such as promotion of breastfeeding, age-appropriate texture progression for weaning, food groups and the important of iron-rich foods.

### Statistical analysis

Analysis will be done by intention-to-treat. Baseline characteristics of participants in the control and intervention arms will be summarised. The primary outcome will be seizure count in the final 2 weeks of the intervention period and in the baseline assessment period. Data will be analysed using a Poisson mixed model to account for clustering by centre (synonymous with therapist). The randomised allocation will be entered into the model as a fixed effect as will an indicator of time point (baseline or end of study), whilst the centre will be included as a random effect. Analysis of secondary outcomes (those seizure free and responders) will be analysed using random-effects logistic models – centre being the random effects and randomised group a fixed effect. The process outcomes relating to tolerability and medium-chain fatty acids in the KD group will be analysed using random-effects modelling. Therapist effects will be investigated further in supportive analyses [7, 37].

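### The sample size assumes dietitian clustering in the KD arm only, but the stated models carry one centre effect common to both arms; if the assumed ICC is real, the standard error is about 10% too small

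*Protocol article*

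**What the plan says.** The Sample size section of the protocol article treats the trial as partially nested. After arriving at 68 per group, it applies "inflation for a therapist effect (dietitian) to one group". The KD arm becomes 92 and the AED arm stays at 68. The factor, 1.35, is reached by "assuming nine centres, with an average cluster size of eight and an intracluster correlation coefficient (ICC) of 0.05".

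The Statistical analysis section gives the primary analysis as a Poisson mixed model of baseline and end-of-treatment seizure counts. Its purpose includes handling clustering by centre, which the article equates with therapist. Allocation and time point are fixed effects, "whilst the centre will be included as a random effect". The binary secondary outcomes use logistic models with centre as the random effect and group as the fixed effect. No KD-only term, centre-by-arm term or arm-specific variance is stated for any of them. The section adds: "Therapist effects will be investigated further in supportive analyses".

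**The concern.** Both arms are recruited within the same centres. A centre effect common to both arms moves KD and AED children up or down together, so it largely drops out of the comparison between them. A dietitian effect that acts only on KD children is different: it is a treatment effect that varies by centre. A shared centre term cannot represent it. In addition, the primary model shares that term with baseline counts, which were recorded before any dietitian had acted.

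The variance that justified the 92:68 split is therefore mostly absent from the standard error of the primary comparison. If that variance exists at the planned size, the primary interval is too narrow and the p-value too small. The responder and seizure-free models have the same weakness. Supportive therapist analyses do not repair the primary standard error.

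**Working it through.** **Inputs (Sample size section):** "mean percentage change in seizures from baseline of 62% (SD 45) in the KD group"; control mean 90% with SD 50; "at 90% power and 5% significance" (taken as two-sided); 10% dropout; nine centres, cluster size 8, ICC 0.05. From Deliverability and feasibility: one centre is expected to supply 28 of 84 children a year, which is one third.

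**1. The plan's own figures reproduce.**
- n per arm = (1.960 + 1.282)² × (45² + 50²) / 28² = 60.6, so 61.
- 61 / 0.9 = 67.8, so 68.
- Design effect = 1 + (8 − 1) × 0.05 = 1.35; 68 × 1.35 = 91.8, so 92.
- With 20% dropout, SE = √(45² × 1.35/73.6 + 50²/54.4) = 9.12 and power is 86.7% (stated: 86%).

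The sample size is therefore not in question. The mismatch lies between it and the stated model.

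**2. True SE with KD-only clustering, 10% dropout (83 KD, 61 AED).** The total KD variance is held at 45² = 2025, with 5% of it between centres. S is the sum of squared centre shares.

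SE² = 0.95 × 2025/83 + 0.05 × 2025 × S + 2500/61

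- Nine equal centres, S = 1/9: 23.18 + 11.25 + 40.98 = 75.41, so SE = 8.7.
- One centre with a third of the children and eight with 1/12 each, S = 1/9 + 8/144 = 1/6: 23.18 + 16.88 + 40.98 = 81.04, so SE = 9.0.

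**3. SE that the shared-effect model reports.** The centre term cancels, and what remains is roughly the pooled residual variance: (83 × 1923.75 + 61 × 2500)/144 = 2168. Then √(2168 × (1/83 + 1/61)) = 7.85. Simulated REML fits gave 7.9.

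**4. Implied type I error with a 1.96 cut-off.**
- Equal centres: 7.9/8.7 = 0.91; 1.96 × 0.91 = 1.78; two-sided probability 7.5%.
- Unequal centres: 7.9/9.0 = 0.88; 1.96 × 0.88 = 1.72; two-sided probability 8.5%.

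**5. Simulation checks, no treatment effect, KD-only ICC 0.05 unless shown.**

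| Setting | Model | Reported SE / true SE | Type I error |
|---|---|---|---|
| Linear, 83/61, equal centres | shared | 7.92 / 8.74 | 7.4% |
| Linear, 83/61, one third in one centre | shared | 7.89 / 8.95 | 8.5% |
| Linear, 92/68, equal, ICC 0 | shared | ratio 0.99 | 6.0% |
| Linear, 92/68, equal | shared | ratio 0.90 | 7.8% |
| Linear, 92/68, one third in one centre | shared | ratio 0.87 | 8.9% |
| Linear, 92/68, equal | KD-only | ratio 1.01 | 5.7% |
| Linear, 92/68, one third in one centre | KD-only | ratio 1.00 | 5.9% |
| Poisson, 92/68, equal, ICC 0 | shared | ratio 0.98 | 5.3% |
| Poisson, 92/68, equal | shared | ratio 0.90 | 8.1% |

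The 83/61 rows used 3,000 runs, the linear 92/68 rows 2,000 and the Poisson rows 1,500. The Poisson runs used end-of-treatment counts only, with an assumed mean of 8 (four seizures a week over two weeks). A further set of 2,500 linear trials at 83/61 gave 7.1% (equal centres) and 9.8% (unequal), so single simulated figures should be read to within about a point.

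**6. Sensitivity.** At ICC 0.02, type I error is 6–7%. With 14 equal centres (an assumption) it is 6.7%, or 7.8% if one centre holds a quarter of the children. At ICC 0.10, twice the planned value, it is 10.5% to 12.5% in the linear 92/68 runs.

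**The case against.** The strongest reply is that the article never writes the word intercept, says the model is meant to account for therapist clustering, and may leave the exact random structure to an analysis plan that is not shown. That possibility is real. Even so, one centre random effect with no arm-specific term is, on its plain reading, a shared intercept, and the article does state this as the primary structure.

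Second, the problem exists only if the dietitian effect does. ICC 0.05 is a planning assumption. Treatment procedures describes a diet manual, a dietitian workshop and cross-site monitoring, all of which should reduce it, and Trial status says more centres are being opened. This stands, and the conclusion is conditional for that reason. Third, part of the excess comes from using 1.96 with few centres: the error is about 5.5–6% even at ICC 0. The missing term itself therefore accounts for about 2–3 points. Fourth, the points-scale figures come from a linear analogue, not the planned Poisson model on baseline and end counts. The Poisson check supports the direction and the approximate size, but only on end counts.

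A reader might also infer that the 24 additional KD children serve no purpose, or that therapist effects are ignored. The article supports neither: those children still reduce the sampling variance of the KD mean, and therapist effects are to be examined in supportive work.

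**Conclusion.** The point holds in conditional form. The design assumes clustering in one arm, and the models as stated do not represent it. If the ICC of 0.05 is real, with about nine centres, the standard error is about 10% too small (9% with equal centres, 12% with a third of children in one centre). Type I error is then roughly 7–9%, against about 5.5–6% with no KD-specific effect. This is a moderate bias in the primary comparison.

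It would be too strong to say that the primary standard error will be too small whatever the data show. With a negligible dietitian effect the shared model is close to nominal, and the documents give no evidence on the true ICC. The conclusion rests on reading the stated random effect as a single shared intercept, on the linear analogue with the protocol's SDs, and on a 1.96 cut-off.

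**What to change.** In the primary Poisson model and in the responder and seizure-free logistic models, specify a centre (therapist) random effect that applies to the KD arm (partially nested). Add a shared centre intercept as well if it can be estimated. When the simulated data had both kinds of centre effect at 0.05, the KD-only term alone was slightly conservative (SE ratio 1.09, type I error 4.5%), while the shared term alone stayed anti-conservative (0.91, 7.9%).

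State a small-sample allowance for about nine centres and name the method, since the usual degrees-of-freedom corrections are built for linear mixed models. Pre-specify a fallback for a variance component on the boundary or a model that does not converge. Keep the shared-effect model as a sensitivity analysis.

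The sample size stays at 160. The cost is a somewhat wider interval, which the 1.35 inflation was meant to cover, and a risk of convergence problems with so few centres. The change should be fixed before the outcome data are analysed.

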The epilepsies in this age group also remain poorly defined entities; very few can be classified into an epilepsy syndrome and diagnosis of underlying cause remains difficult. Over 50% of infants presenting with seizures will have infantile spasms [3]. This affects approximately 1 in 2000 infants. First-line treatment options (corticosteroids or vigabatrin) lead to seizure freedom in up to 70% of cases [9] but side effects limit their duration of use and relapse rates are substantial (40%) [10]. Further, those who fail these treatments are limited in their treatment options. Of the remaining types of epilepsy, the majority are resistant to medication. There is little evidence on which to base our decisions on specific AED use in this young age group. Epidemiological data have shown this group to be the least likely to achieve longer-term remission of up to 2 years [11].

The ketogenic diet (KD) is a high-fat, low-carbohydrate diet designed to mimic the effects of starvation on the body. The main energy intake is fat, which is converted to ketones in the body and used as an energy source. The classical KD is based on an intake of long-chain fat, usually in a ratio of 3 or 4 g of fat to 1 g of carbohydrate and protein. The medium-chain triglyceride (MCT) KD utilises MCT fat, which generates more ketones per calorie compared to long-chain fat, theoretically allowing greater dietary intake of carbohydrate. More liberal diets have also been utilised, including the Modified Atkins Diet and low-glycaemic-index treatment, which are high in fat, low in carbohydrate but with unlimited protein [12, 13].

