The randomisation schedule will be independently generated and held by Sealed Envelope™. Allocations will be released by email to the coordinating centres once the investigator or research nurse has entered eligible participant information into the web-based randomisation service. Participants will be allocated to either the KD or further AED arm using a simple, concealed, randomisation method. Randomisation will aim to achieve 92 in the KD group versus 68 participants in the further AED arm (see calculation in ‘Sample size’ section). An Enrollment Log will be maintained to keep records of the screened and randomised patients at each site. Withdrawn patients will not be replaced and replacement numbers will not be issued. Whilst it will not be possible to blind participants to their treatment allocation, efforts will be made to minimise expectation bias by emphasising in the trial literature that the evidence supporting the KD for seizure control is currently limited.

A second assessment (4 weeks after start of treatment) will include clinical review and a tolerability questionnaire (modified Hague Scale of Side Effects – see Additional file 2). Assessments will be repeated at 8 weeks after the start of treatment including clinical review, administration of the Infant and Toddler Quality of Life Questionnaire, the tolerability questionnaire, and biochemical investigations. After the 8-week assessment, according to patient’s clinical response to treatment with regards seizure outcome and tolerability, the KD (diet group) or AED (standard AED group) will then be continued or changed. Those in the AED group who have failed to achieve seizure control at the 8-week assessment will then be offered the KD outside the context of the trial. Those on the KD who have failed to achieve seizure improvement at the 8-week assessment will continue with medical management, as per clinician decision. All participants will be followed up for 12 months following randomisation for retention, seizure outcome and neurodevelopmental status. See Fig. 1 (Standard Protocol Items: Recommendations for Interventional Trials (SPIRIT) figure: schedule of enrollment, interventions and assessments) and Additional file 3 for the SPIRIT 2013 Checklist (recommended items to address in a clinical trial protocol and related documents).

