### Outcomes

The primary outcome will be the number of seizures experienced during weeks 6–8 compared to the number of seizures in the baseline period.

Secondary outcomes will include (at 8 weeks):Number of children seizure freeResponder rate, defined as the number showing more than a 50% improvement in seizure frequency compared to baseline (taken as the mean daily seizure frequency over the observation baseline period immediately preceding the 8-week review)Tolerance to KD as assessed by side effect questionnaire and blood resultsRelationship between medium-chain fatty acids and seizure control

Secondary outcomes will also include (at 12 months):Retention on treatment (the number of participants who remain on the KD, or the prescribed AED, at 12 months)Quality of life (as measured by the Infant Toddler Quality of Life Questionnaire)Neurodevelopmental outcome (as measured by the Vineland Adaptive Behaviour Scales)

Plasma profiles of medium-chain fatty acids will be evaluated at baseline and at 8 weeks. Assessment of mitochondrial function (respiratory-chain enzymes) and enrichment (citrate synthase) will be determined in white cells and platelets. The effect of specific ratios of medium-chain fatty acids, to mimic patient plasma profiles, upon neuronal mitochondrial function/enrichment (biochemical plus electron microscopy studies) will be documented. Additionally, such fatty acid profiles will be studied, with regards to antiepileptic effect, in an established in vitro (hippocampal slice) model.

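### Randomisation is simple and the stated logistic models have no baseline term, so differences in baseline seizure frequency and epilepsy type go unadjusted, at a cost in precision and conditional validity

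*Protocol article*

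**What the plan says.** Under Methods/design, participants are allocated "using a simple, concealed, randomisation method". No stratification or minimisation factor is named. The target is unequal: "Randomisation will aim to achieve 92 in the KD group versus 68 participants in the further AED arm".

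Under Statistical analysis, the models are given term by term. The logistic models for seizure freedom and response are described as "centre being the random effects and randomised group a fixed effect". The primary Poisson mixed model has allocation as a fixed effect, "as will an indicator of time point (baseline or end of study", and a random centre effect. Its outcome is the "seizure count in the final 2 weeks of the intervention period and in the baseline assessment period". Of other baseline information the section says only this: "Baseline characteristics of participants in the control and intervention arms will be summarised".

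Under Outcomes, a responder is a child with "more than a 50% improvement in seizure frequency compared to baseline". Seizure freedom is a plain count of children without seizures at 8 weeks.

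On epilepsy type, the Background states: "Over 50% of infants presenting with seizures will have infantile spasms". It separates these infants from those with other epilepsies, most of which it calls drug resistant. The inclusion criteria have a special clause for spasms, and the control drug is chosen partly by epilepsy syndrome.

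**The concern.** The article treats epilepsy type as important in its background, in eligibility and in the choice of control drug, but neither the allocation nor any stated model takes account of it. Seizure frequency also varies widely at entry, and the seizure-freedom model ignores it.

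Two things are at stake. The first is precision: a prognostic factor left out of a model stays in the unexplained variation and costs power. The second is conditional validity: once a particular imbalance has occurred, an unadjusted comparison no longer has its nominal error rate for that trial. There is also a practical risk. In an open-label trial, covariates added after an imbalance has been seen are open to challenge, whereas covariates named in advance are not.

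**Working it through.** **Inputs from the article.** Target arms of 92 and 68 (Methods/design, Sample size). Dropout 10% (Sample size). Entry at four or more seizures a week (Inclusion criteria). Shorter baseline for children with more than two seizures a day (Methods/design). Response of 38% on diet in the earlier trial in children aged 2 to 16 (Background).

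**Assumptions, not in the article.** Spasms share *p* of 30% to 70%; control response of 20%; odds ratio for spasms of 2, 4 or 6.

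**1. The plan's own numbers.** Pooled variance is (45² + 50²)/2 = 2262.5. Then n = 2 × (1.96 + 1.28)² × 2262.5 / 28² = 60.6, so 61 per group. 61/0.9 = 67.8, so 68. The design effect is 1 + (8 − 1) × 0.05 = 1.35, and 68 × 1.35 = 91.8, so 92. The total is 160, and the stated sizes reproduce.

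**2. Chance imbalance in a binary factor.** The SD of the difference in proportions is √[p(1 − p)(1/92 + 1/68)], with the target arm sizes taken as met.

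| Assumed share | SD | P(above 10 points) | P(above 15 points) |
|---|---|---|---|
| 50% | 8.0 points | 21% | 6% |
| 30% or 70% | 7.3 points | 17% | 4% |

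**3. Spread in baseline seizure frequency.** Entry starts at 4 a week. More than two a day is more than 14 a week, and 14/4 = 3.5. Eligible children therefore differ at least 3.5-fold. The responder outcome divides by the child's own baseline; seizure freedom does not. The article gives no figure linking baseline rate to the chance of seizure freedom, so no power gain is computed for this term.

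**4. Power for response, with and without spasms in the model.** Completers are 0.9 × 92 = 83 and 0.9 × 68 = 61, in total 144. Response is 38% v 20%, the spasms share is 50%, and there is no centre effect. With 5,000 simulated trials per row:

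| Odds ratio for spasms | Unadjusted | Adjusted | Gain |
|---|---|---|---|
| 1 (not prognostic) | 67% | 66% | −1 point |
| 2 | 65% | 65% | 0 |
| 4 | 65% | 68% | 3 points |
| 6 | 66% | 72% | 6 points |

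A separate run of 1,500 trials per row gave 66% v 66%, 66% v 70% and 66% v 70% at odds ratios of 2, 4 and 6, which agrees within simulation error.

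**5. Type I error.** Overall, it was simulated on a continuous scale (20,000 trials of 160, spasms share 50%, a gap of 20 or 40 points of baseline seizures between children with and without spasms). The unadjusted test rejects in 4.8% and 5.2% of trials. Among trials with an imbalance above 10 points it rejects in 5.9% and 9.5%; adjusted, in 5.2% and 4.8%. On the binary scale, given the same imbalance, the unadjusted rates are 5.9% (fourfold) and 7.7% (sixfold), against 4.5% and 5.5% adjusted.

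**The case against.** The strongest objection is scope. Covariates are commonly left to the SAP, which is not shown, and one condensed paragraph does not rule them out. An unadjusted randomised comparison is valid. This stands in part: the point is about the models as stated, and an SAP may already cover it. But the article does list its model terms, and a better list is available.

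Four stronger readings are tempting, and the documents do not support them.

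- *More than half of the trial's children have spasms.* The Background figure describes infants presenting with seizures. The trial enrols children who have failed two drugs, and the article says first-line treatment stops seizures in up to 70% of spasms cases, so the mix may differ. The trial share is unknown.
- *Spasms are a proven strong predictor here.* The Background contrasts first-line response. It gives no difference after two failures, so the odds ratios above are assumed.
- *Imbalance biases the result.* Chance imbalance under randomisation is not bias. Overall type I error stays near 5%; only the error rate given an imbalance moves.
- *The plan ignores baseline.* The baseline count is one of the two responses in the primary model, and response is defined against each child's own baseline. The gap is complete only for seizure freedom.

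It is also fair to say that the 38% comes from older children, that the control rate in that trial was 6% rather than 20%, and that response is a secondary outcome for which the trial was not sized.

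**Conclusion.** The point holds as one of efficiency and robustness, limited to the two logistic models. It is clearest for seizure freedom, which is modelled with no baseline term although children enter with at least a 3.5-fold range of seizure rates. For epilepsy type, the chance of an imbalance above 10 points is about one in five or six. The gain in power runs from none to about 6 points, depending on how prognostic spasms are after two drug failures, which the article does not say. If they are not prognostic at all, adjusting costs about 1 point. The unadjusted analysis would still be valid.

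The point does not extend to adding a spasms-by-time term to the primary model. No allocation-by-time term is stated there, so such a term would not supply or sharpen the treatment contrast.

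**What to change.** Before the outcome data are seen, state in the SAP that the logistic models for seizure freedom and response will include log baseline seizure rate and infantile spasms (yes or no) as fixed effects, alongside randomised group and random centre. At the time of the article 29 children had been randomised, so there was still time to do this.

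The cost is mainly wording. Baseline seizure counts are collected for every child. Spasms status should be obtainable from the baseline seizure history, although the article does not list it as a separate item, so this should be confirmed on the case report form.

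There are two downsides. The odds ratio becomes conditional on the covariates and is not directly comparable with an unadjusted one. And if few children become seizure free, two extra terms plus a random centre effect may make the fit unstable. Report the unadjusted estimate, or one standardised over the covariates, next to the adjusted one, and say in advance which takes precedence.
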